#### **4.2.4 Analysis of primary endpoint**

The incidence of POD between the two groups was compared with  $\chi^2$  tests, and the odds ratio (OR) with 95% CI was calculated.

The time-to-event analytic approach was also used to compare the cumulative incidence of POD between the groups. Kaplan-Meier analysis was used to estimate the cumulative incidence of POD, and difference of incidence between groups was compared with the log-rank test.

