### **3.4 Randomization Procedure**

Patients were assigned by computer to either cognitive training or routine care in a 1:1 ratio stratified by

study site with random blocking. The computer-generated randomization schema was developed by an unblinded statistician and allocation was concealed from study investigators in sequentially numbered sealed opaque envelopes.

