## **4. Statistical Analysis Plan**

### **4.1 Sample size calculation**

In a previous study of patients recovering from coronary artery bypass graft surgery, the incidence of postoperative delirium was 35%.[47] We powered our trial to detect a 50% relative reduction in delirium from a 35% baseline consequent to cognitive training. 96 patients were required in each group for a two-tailed  $\alpha=0.05$  with 80% power. Assuming a potential dropout rate of 10%, we included a total of 214 patients (107 in each group).

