### 4.2.3 General considerations

**Data set:** The assessment of primary endpoint will be performed based on m ITT set. The per protocol set is mainly used for sensitivity analysis. Patients who engaged in cognitive training for 3 or more hours were considered to have met our minimum compliance threshold, and included in per protocol set. The establishment of this threshold is derived from the results of our preliminary meta-analysis.

**Covariates and subgroup analysis:** Subgroup analysis will be performed and the subgroup analysis will be carried out as exploratory. To evaluate treatment effect heterogeneity on the primary outcome, predefined subgroup analyses were performed based on surgical methods, age, sex, education level, and baseline cognitive function. Interactions between cognitive training and each variable were assessed by adding interaction terms to the logistic regression model.

**multi-center effect analysis:** This is a multicenter RCT study, and there may be center effects among different centers. The logistic regression models will be used to control the multi-center effect, with the different centers set as fixed effect.

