#### **4.2.5 Analysis of other endpoints**

For secondary and exploratory endpoints, continuous data will be presented as means (SDs) or median (IQRs), as appropriate. The secondary endpoint followed no Gaussian distribution, will be presented as median (interquartile range) and tested by Mann-Whitney U test. POCD was defined as a 1 standard deviation decline in MoCA score on postoperative day 7, or at discharge if earlier, compared to baseline. This definition aligns with previous definitions of POCD and current recommendations for defining POCD or delayed neurocognitive recovery. [48,49] Mantel-Haenszel  $\chi^2$  and Cuzick tests assessed a potential dose-response relationship between the total hours of cognitive training and incidence of delirium. Analyses of delirium duration and delirium-positive days were conducted using the Zero-inflated Poisson regression model. Regarding the assessment of delirium severity, ordinal logistic regression model was used to model no delirium, delirium and severe delirium. Additionally, a post-hoc analysis incorporating study site, age, surgical technique, baseline educational level and cognitive function of the participants was conducted.

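### Randomisation is stratified by site, but the primary test ignores site, and the protocol is inconsistent about the role of site adjustment

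*Protocol*

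**What the plan says.** Four places in the protocol bear on this.

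- **Section 3.4** allocates 1:1, stratified by "study site with random blocking".
- **Section 4.2.4** is headed as the analysis of the primary endpoint: "The incidence of POD between the two groups was compared with" chi-square tests, with an odds ratio and 95% confidence interval. It adds a Kaplan-Meier and log-rank comparison of the same event. Neither analysis uses site.
- **Section 4.2.3** accepts that centres may differ and states: "The logistic regression models will be used to control the multi-center effect, with the different centers set as fixed effect". It does not say for which endpoint, or whether this result is primary or supportive.
- **Section 4.2.5**, on other endpoints, ends with "a post-hoc analysis incorporating study site, age, surgical technique, baseline educational level and cognitive function of the participants was conducted". No endpoint is named there either.

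The sample size in section 4.1 rests on two crude proportions: "We powered our trial to detect a 50% relative reduction in delirium from a 35% baseline", and "96 patients were required in each group for a two-tailed" 5% test with 80% power.

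**The concern.** Site adjustment is promised in 4.2.3, absent from the primary analysis in 4.2.4 and called post hoc in 4.2.5. An analysis set out in the protocol cannot also be post hoc, and nothing ranks the site-adjusted result against the crude one. The two odds ratios also estimate different quantities, one conditional on site and one marginal, so they will differ somewhat even when both are correct.

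Stratifying by site balances the arms within site. If delirium rates differ between sites, the Pearson variance still includes that between-site variation, although the design has removed it from the treatment comparison. The crude test is then too cautious.

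A smaller point concerns the effect measure. The trial is powered on a relative risk reduction, but the only effect measure given a confidence interval is an odds ratio, which at this incidence is numerically well away from the risk ratio.

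**Working it through.** **1. The plan's own sample size.** Inputs from section 4.1: p1 = 0.35, p2 = 0.175 (a 50% relative reduction), two-sided alpha 0.05, power 80%, dropout 10%.

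Unpooled two-proportion formula: n = (1.960 + 0.842)² × [p1(1−p1) + p2(1−p2)] / (p1−p2)² = 7.849 × (0.2275 + 0.1444) / 0.030625 = 95.3, rounded up to 96 per arm. Then 96 / 0.9 = 106.7, rounded up to 107 per arm and 214 in total. The stated figures reproduce. The pooled formula gives 99, and power at 96 per arm by that formula is 79.2%. The sample size therefore belongs to the unadjusted test, and that test has its planned power.

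**2. Why the crude test is conservative.** The number of sites and their variation are not given, so they are assumed. Take four equal sites with an overall rate of 35% in both arms (no treatment effect). The Pearson test uses p(1−p) = 0.35 × 0.65 = 0.2275. With allocation balanced within site, the true variance is the average of p_k(1−p_k) over sites.

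- Site log-odds SD 0.5, rates 20.8, 30.1, 38.5 and 50.6%: average 0.2155, ratio 0.947, square root 0.973. The critical value is in effect 1.960 / 0.973 = 2.014, so true type I error is 4.4%.
- SD 1.0, rates 10.7, 24.2, 40.5 and 64.6%: average 0.1872, ratio 0.823, square root 0.907. The critical value is in effect 2.161, so type I error is 3.1%.

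**3. Simulation.** 20,000 trials per scenario, 96 per arm, 2, 3, 4 or 6 equal sites, overall rates fixed at 35% and 17.5%, equal allocation within site. The crude chi-square is compared with Cochran-Mantel-Haenszel (CMH) by site, which stands in for logistic regression with site as fixed effect. Ranges are over the numbers of sites.

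| Site log-odds SD | Power, crude | Power, CMH | Type I error, crude | Type I error, CMH |
|---|---|---|---|---|
| 0 | 79.5–79.9% | 79.5–79.8% | 4.9–5.2% | 4.8–5.2% |
| 0.25 | 79.8–80.0% | 80.0–80.2% | 4.7–5.1% | 4.9–5.3% |
| 0.5 | 80.1–80.3% | 81.1–81.3% | 4.3–4.7% | 4.9–5.2% |
| 0.75 | 80.5–81.2% | 82.9–83.6% | 3.6–4.0% | 4.7–5.2% |
| 1.0 | 81.2–81.8% | 85.2–85.6% | 3.0–3.1% | 4.9–5.1% |

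The power forgone is 0 to 1 point up to SD 0.5, about 2.5 points at SD 0.75 and about 4 points at SD 1.0. At SD 1.0 control rates run from 14.5% to 55.5% with two sites and from 9.1% to 68.7% with six, which is wide.

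**4. Effect measures.** The planned risk ratio of 0.50 corresponds to a crude odds ratio of (0.175/0.825) / (0.35/0.65) = 0.394. The site-conditional odds ratio giving the same overall rates is about 0.38 at SD 0.5 and 0.34 at SD 1.0.

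**5. Expected events.** 96 × 0.35 + 96 × 0.175 = 33.6 + 16.8 = 50.4.

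**The case against.** The best defence is that an unadjusted comparison is valid in a randomised trial, that the sample size was computed for exactly this test, and that any error is on the cautious side, so a positive result would not be undermined. All of that stands. Hierarchy among models is also often left to a separate SAP, and one may exist here. That helps less than usual, because section 4 carries the title of a statistical analysis plan and its own statements disagree.

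Four stronger readings are tempting, and the protocol does not support them.

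- **The trial loses power against its plan.** It does not. The crude test had about 80% power or slightly more in every scenario; what is given up is a possible gain.
- **There are several conflicting primary analyses.** Only 4.2.4 is headed as primary. The model in 4.2.3 is a general consideration without a rank, and the one in 4.2.5 sits among other endpoints.
- **Only an odds ratio will be reported.** Sections 4.2.2 and 4.2.3 require frequencies and percentages, and 4.2.4 adds Kaplan-Meier incidence, so both groups' risks will be visible. What is not prespecified is a confidence interval for the risk ratio or the risk difference.
- **Age and baseline MoCA must enter the primary model.** The background calls age a significant risk factor, but the protocol gives no measure of how well these variables predict delirium. Any stated gain would rest on assumed values.

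**Conclusion.** The point holds as an inconsistency and an avoidable inefficiency. The primary test omits the stratification factor, and the protocol gives site adjustment three different standings. The statistical cost runs from nil to a type I error of about 3.1% and about 4 points of power forgone, the upper end requiring very different sites. At moderate variation (SD 0.5) it is a type I error of about 4.4% and about 1 point of power. These figures rest on assumed equal sites, 2 to 6 in number, with assumed variation. The contradiction in the text does not depend on them.

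This should be fixed because the change costs almost nothing and settles in advance which result is primary. It is not a flaw that must be cured for the trial to be valid.

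**What to change.** 1. In 4.2.4, name one site-stratified primary analysis: either CMH by site, or logistic regression with arm and with site as fixed effect. Point 4.2.3 to it, with the endpoint stated.
2. Label the crude chi-square and the log-rank test as supportive.
3. Beside the odds ratio, report a risk ratio and a risk difference with 95% confidence intervals, since the trial is powered on a relative risk reduction. State whether the odds ratio is conditional on site or marginal.
4. In 4.2.5, replace the post hoc label with prespecified supportive covariate-adjusted analysis, and name its endpoint.

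Adding age and baseline MoCA to the primary model is optional. With about 50 expected events and an unknown number of site terms, a larger model may become sparse; CMH by site is the simpler choice.

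The cost is wording only. Site is already recorded as the stratification factor, and no further patients are needed. One consequence to accept is that the site-conditional odds ratio differs slightly from the crude one (about 0.38 at SD 0.5 and 0.34 at SD 1.0, against 0.39), which is a further reason to report the risk ratio and risk difference.

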### **3.7.3 Postoperative outcomes**

#### **The primary outcome:**

The incidence of delirium from postoperative day 1 to postoperative day 7 or before discharge, whichever occurred first.

Diagnosis of POD was based on the results of CAM or CAM-ICU twice daily, [42,43] specifically from 08:00 to 10:00 and from 18:00 to 20:00. All blinded researchers were trained in CAM/CAM-ICU assessment and the consistency among research members was reached. When there is a contradiction between the diagnosis obtained by the scale and the diagnosis of the psychiatrist, when there are still differences after consultation, the diagnosis of the psychiatrist shall prevail. In order to prevent missed diagnosis, we should communicate with the medical staff in the ward in time. After the patient is selected, the family member or escort staff should be informed, and the investigator should be informed of the evaluation of delirium in time when any abnormal performance of the patient's mood, consciousness, cognition and so on is found. Comprehensive reviews of progress notes, nursing documents, and medical records were conducted by blinded investigators to identify instances of delirium between postoperative day 1 and 7, employing a chart-based delirium identification instrument. [44,45] Patients diagnosed with delirium through any of the aforementioned methods were considered to have experienced delirium on that particular day. When postoperative delirium is found, the subject should communicate with the competent physician and decide on further diagnosis and treatment. If the patient's performance was normal 7 d after operation, the visit ended, while the patient with continuous delirium was followed up

until normal or discharged.

Outcomes were assessed by investigators specifically trained in recognition and assessment of delirium.

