**Secondary outcomes:**

- (1) cumulative incidence of POD
- (2) incidence of severe delirium, evaluated with the Memorial Delirium Assessment Scale (MDAS)[46]
- (3) postoperative cognitive dysfunction (POCD) on postoperative day 7 or at discharge if earlier, used by the Montreal Cognitive Assessment (MoCA) (range, 0 [worst] to 30 [best]), defined as a 1 standard deviation decrease from baseline in Montreal cognitive assessment score at postoperative day 7 or discharge.
- (4) cognitive function one month after surgery, used by the Revised Telephone Interview for Cognitive Status (TICS-m) (range, 0 [worst] to 50 [best])
- (5) 30-day all-cause mortality
- (6) durations of intensive care unit (number of days in the intensive care unit from the end of operation to discharge) and postoperative hospital care.
- (7) elapsed time from the end of surgery to delirium onset
- (8) duration of delirium (defined as the period between the first and last delirium-positive day, even if there were non-delirious days in between)
- (9) the total number of delirium-positive days in patients who developed delirium
- (10) cognitive function at three time points (baseline, preoperative, postoperative day 7 or at discharge if earlier. was used to assess early POCD on the seventh day after surgery or at discharge and cognitive function at any time points before or after surgery.
- (11) Postoperative intubation time, defined as duration from the end of the procedure to extubation.
- (12) intensive care unit readmission within 30 days after surgery.
- (13) Number of days alive and out of the hospital within 30 days. (The sum of the number of days patients were alive and not in the hospital within 30 days after surgery. It is calculated as 30 days minus the total number of days in hospital after surgery (maximum 30 days, minimum 0 days). If the patient is not hospitalized from 00:00 to 24:00 in a day, the number of days without hospitalization can be counted; After discharge, patients were hospitalized for a second time, and the second hospitalization time was also included in the total number of days in hospital. The patient died within 30 days of surgery. DAOH 30 is 0 days; If the patient was not discharged 30 days after surgery, DAOH 30 was recorded as 0 days.)

All outcomes were assessed by investigators masked to patient allocation.

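### Kaplan-Meier and log-rank are named for the cumulative incidence of delirium although observation stops at discharge; if discharge is censored, the curve sits at or above the in-hospital incidence

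*Protocol*

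**What the plan says.** The primary outcome in Protocol section 3.7.3 is delirium from postoperative day 1 to "postoperative day 7 or before discharge, whichever occurred first". Section 4.2.4 compares this binary incidence by a chi-square test and gives an odds ratio with a 95% confidence interval.

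Under the same heading, section 4.2.4 adds a time-to-event analysis: "Kaplan-Meier analysis was used to estimate the cumulative incidence of POD, and difference of incidence between groups was compared with the log-rank test". The quantity it estimates, "cumulative incidence of POD", is item 1 of the secondary outcomes in section 3.7.3. Neither section gives a censoring time or says how discharge before day 7 enters the curve, and no competing-risk method is named.

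On deaths, section 3.2.3 makes death before the primary outcome assessment a drop criterion. The modified intention-to-treat exclusions in section 4.2.1 do not mention death.

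**The concern.** Under the primary definition, a patient who goes home on day 5 without delirium is a completed non-event. Under Kaplan-Meier with follow-up ending at discharge, the same patient is censored and is implicitly given the later delirium hazard of those still in hospital. Those still in hospital are plausibly sicker, so censoring at discharge is plausibly informative. The curve then estimates the delirium risk if everybody stayed seven days, which is a different quantity from the proportion who become delirious in hospital.

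Two consequences follow. The day-7 value of 1-KM need not agree with the percentages in the primary table, and any disagreement is upward. And section 4.2.4 presents log-rank as a comparison of incidence, whereas with competing discharge it compares the rate of first delirium among patients still under observation.

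The placement adds some confusion: a secondary outcome has its only stated analysis under the primary-endpoint heading.

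**Working it through.** **The plan's own figure.** Section 4.1 says: "We powered our trial to detect a 50% relative reduction in delirium from a 35% baseline", and "96 patients were required in each group for a two-tailed" test at 0.05 with 80% power. The unpooled two-proportion formula gives

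n = (1.960 + 0.842)² × (0.35×0.65 + 0.175×0.825) / 0.175² = 95.3, rounded up to 96 per group.

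With 10% dropout, 96/0.90 = 106.7, so 107 per group and 214 in total. Both figures reproduce. The sample size therefore rests on the binary comparison, not on the log-rank test.

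**Method for the gap.** Days 1 to 7 are treated as discrete. Let h_d be the delirium hazard on day d among patients still in hospital and event-free, and let G_d be the probability of not yet having been discharged or died by the end of day d.

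- 1-KM = 1 − Π(1 − h_d).
- In-hospital incidence = Σ h_d × (fraction still in hospital and event-free at the start of day d). This equals the Aalen-Johansen cumulative incidence with discharge and death as competing events.

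If onset without discharge would total p with daily shares s_d, the second line becomes Σ p × s_d × G_(d−1), and 1-KM equals p.

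**Inputs.** From section 4.1, p is 35% (control) and 17.5% (training), used here as the value of 1-KM. Everything else is assumed, because the protocol gives no discharge or early-death rate:

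- Onset front-loaded (30, 30, 20, 10, 5, 3, 2% of onsets on days 1 to 7), in line with the typical 24 to 72 hours in section 1; or flat (one seventh each day).
- Discharge of event-free patients: 5% at the end of days 5 and 6 (1 − 0.95² = 10%); 10, 12, 12% at the end of days 4 to 6 (1 − 0.90×0.88×0.88 = 30%); or 26% at the end of each of days 4 to 6 (1 − 0.74³ = 59%, about 60%).
- Death: 0, 0.3 or 0.7% per day (0, about 2% and about 5% over seven days).

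**One case by hand.** Control arm, front-loaded onset, 30% discharged, no deaths. Days 1 to 4 contribute 10.5 + 10.5 + 7.0 + 3.5 = 31.5. Day 5 contributes 1.75×0.90 = 1.575, day 6 1.05×0.792 = 0.832 and day 7 0.70×0.697 = 0.488. The total is 34.4% against 1-KM of 35.0%, a gap of 0.6 points.

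**Results** (in-hospital incidence in %, gap in points; 1-KM is 35.0 and 17.5 in every row).

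| Onset | Discharged early | Death per day | Control | Gap | Training | Gap |
|---|---|---|---|---|---|---|
| Front-loaded | 10% | 0 | 34.88 | 0.12 | 17.44 | 0.06 |
| Front-loaded | 30% | 0.3% | 34.25 | 0.75 | 17.12 | 0.38 |
| Front-loaded | 60% | 0.7% | 33.34 | 1.66 | 16.67 | 0.83 |
| Flat | 10% | 0 | 34.26 | 0.74 | 17.13 | 0.37 |
| Flat | 30% | 0.3% | 31.68 | 3.32 | 15.84 | 1.66 |
| Flat | 60% | 0.7% | 27.97 | 7.03 | 13.99 | 3.51 |

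With no discharge and no death the gap is zero. The risk ratio is 0.50 in every row on either scale, because discharge and death were set equal in the two arms.

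**A second set of assumptions, single arm, no deaths.** Event-free discharge at the end of days 4, 5 and 6 is 0/10/10% (light, 19% gone), 10/20/30% (moderate, 50% gone) or 30/40/50% (heavy, 1 − 0.7×0.6×0.5 = 79% gone).

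- Falling daily hazards of 12, 10, 6, 4, 3, 3, 3%: 1-KM 34.8% against 34.2, 33.0 and 31.3%. Gaps: 0.6, 1.8 and 3.4 points.
- Hazards rising late, 12, 10, 6, 5, 6, 7, 8%: 1-KM 43.1% against 41.7, 38.9 and 35.2%. Gaps: 1.4, 4.2 and 7.9 points.

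**The case against.** The strongest reply is that the protocol never says discharge is censored. A reader might infer that it is, from the name of the method, but no section states it and the rule may sit in a separate analysis plan. If delirium-free discharged patients are carried to day 7 as event-free, 1-KM equals the crude proportion, apart from deaths and other losses. This stands, and it makes the point conditional. It does not remove the point: section 4.2.4 positively names an estimator and a test, and describes the test as one of incidence, for an outcome whose observation ends at discharge.

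A reader might also infer that early deaths are censored. Section 3.2.3 suggests they may be dropped instead, while section 4.2.1 does not exclude them. That mismatch is a separate matter, and the argument about discharge does not depend on it.

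Nor does the log-rank test become invalid. A comparison of cause-specific hazards is legitimate; only its description as a comparison of incidence is wrong.

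Finally, the size is probably small. Section 1 places typical onset at 24 to 72 hours, before most discharges would occur under the assumed schedules. The gap of about 8 points needs 79% of event-free patients gone by the end of day 6 together with rising late hazards. This also stands.

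**Conclusion.** The point holds in conditional form. If event-free discharge, and any death not dropped, is censored in the ordinary way, 1-KM will be at or above the in-hospital incidence shown beside it, and log-rank will not test a difference of incidence. With early onset as in section 1, the likely gap is about 0 to 2 points in the control arm. It reaches about 3 points with falling hazards and 79% early discharge, and about 7 to 8 points only with heavy early discharge and flat or rising hazards. All these sizes rest on assumed discharge, death and onset patterns.

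A reader might conclude that the primary result is biased. It is not: the chi-square test, the odds ratio and the sample size use the binary outcome and are untouched. A reader might also conclude that the treatment comparison is distorted. That has not been shown. With equal discharge and death in the arms the risk ratio stays at 0.50. Unequal discharge was not calculated, although postoperative stay is itself a secondary outcome, so equality cannot be taken for granted.

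**What to change.** In section 4.2.4, estimate the cumulative incidence of first delirium to day 7 with the Aalen-Johansen estimator, taking event-free discharge and death as competing events, and compare the arms by Gray's test. For discharge, an equivalent course is to state that delirium-free discharged patients stay in the risk set to day 7 as event-free. Log-rank may be kept if it is described as a comparison of cause-specific hazards. Label the whole analysis as secondary outcome 1, supportive of the binary primary comparison.

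The cost is a few sentences and slightly more analysis in R, which section 4.2.3 already plans to use. The discharge and death dates are already needed for the secondary outcomes on length of stay, 30-day mortality and days alive out of hospital.
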